#### Follow-up visit

2.7.4

Following the end of the final treatment, couples need to be followed up for another 12 months to observe the long-term effect of CHM on male factor infertility. The follow-up visit includes:

(1) Follow up whether the female partner is pregnant;(2) At the end of the follow-up, the semen analysis and DFI of male partners will be rechecked.

#### Pregnancy visit (only with conception)

2.7.5

Female partners who become pregnant within 15 months after randomization will have pregnancy visit, which will last until the termination of pregnancy (pregnancy loss or delivery). During the pregnancy visit, the following procedures will be completed.

(1) Blood human chorionic gonadotropin (HCG) test: pregnancy confirmation;(2) Ultrasound examination (Conducted at 6–8 weeks of pregnancy): to access the quantity and of gestational sacs and the placement, as well as the dimensions, presence and size of fetal structures and to record the visualization of fetal heart motion and any pregnancy-related abnormalities;(3) Record pregnancy loss: record biochemical pregnancy, ectopic pregnancy and all other intrauterine pregnancy loss (including spontaneous abortion, missed abortion, selective abortion and stillbirth);(4) Record the confirmed pregnancy complications;(5) After the female partner has given birth, the researcher will obtain a copy of the check list during pregnancy from the obstetrician to determine the pregnancy and delivery process of the female partner and the information of the newborn (whether it is a live birth, gender, weight, length, whether there is a congenital defect, etc.).

### Adverse events

2.8

Participants involved in this study will not encounter major risks. The minor side effects of CHM may be dizziness, vomiting and diarrhea. The majority of these side effects are temporary and mild, which will disappear in a few days. During the study, the subjects will be asked about their drug tolerance, adverse events and serious adverse events will be recorded.

### Outcome measures

2.9

#### Primary outcome

2.9.1

Live birth rate: defined as a delivery taking place after gestation of ≥20 weeks.

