#### Secondary outcomes

2.9.2

(1) Semen parameters

1) sperm concentration: quantity of spermatozoa per unit of volume of semen, 10^6^/mL;

2) morphology: percentage of normal morphology;

3) motility: percentage of motile (including nonprogressive motile and progressive motile);

4) DFI: evaluate using SCSA test.

(2) Conception rate

Conception will be determined by a positive serum β-hCG measurement (β-hCG >10 mIU/mL).

(3) Pregnancy rate

Pregnancy will be characterized as an intrauterine pregnancy with confirmed fetal heart motion via transvaginal ultrasound.

(4) Pregnancy loss rate

Pregnancy loss will be refers to the intrauterine pregnancy lost before 20 completed weeks of gestation.

(5) Pregnancy complications

Including pregnancy diabetes, pregnancy induced hypertension, preeclampsia/preeclampsia, premature birth, congenital malformations, perinatal death, etc.

(6) Reproductive hormone

Including total testosterone, follicle stimulating hormone, luteinizing hormone, estradiol, progesterone, and prolactin.

(7) Adverse events.

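### The primary outcome definition omits the live-born condition, so a stillbirth at or after 20 weeks meets it as written

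*Protocol article*

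**What the plan says.** Three sections of the protocol article bear on how a late stillbirth is classified.

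- Section 2.9.1 (Primary outcome) consists of one sentence: "Live birth rate: defined as a delivery taking place after gestation of ≥20 weeks".
- Section 2.9.2 (Secondary outcomes) defines loss by the same 20-week boundary: "Pregnancy loss will be refers to the intrauterine pregnancy lost before 20 completed weeks of gestation". Its list of pregnancy complications includes "premature birth, congenital malformations, perinatal death, etc".
- Section 2.7.5 (Pregnancy visit) tells staff to record as pregnancy loss, besides biochemical and ectopic pregnancies, "all other intrauterine pregnancy loss (including spontaneous abortion, missed abortion, selective abortion and stillbirth". After delivery they obtain the obstetric record to establish "the information of the newborn (whether it is a live birth, gender, weight, length, whether there is a congenital defect, etc".

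Section 2.5 states that neither researchers nor participants can be blinded. Section 2.11 plans on live birth rates of 2.5% (waitlist) and 12.5% (herbal medicine), with 105 couples per group raised to 125.

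**The concern.** The name of the outcome and its definition do not match. The name says live birth, but the rule asks only for a delivery and a gestational age. The trial's hypothesis concerns live birth, and the article's Discussion calls it a key outcome that earlier studies lack. An analyst or outcome assessor who applies section 2.9.1 word for word would credit a stillbirth at 24 weeks as a success. One who relies on the name or on section 2.7.5 would not.

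That choice should not be left open where staff know the allocation and the control arm is expected to contribute only a handful of events.

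**Working it through.** **1. Where a stillbirth at or after 20 weeks falls**

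| Section | Rule | Late stillbirth is |
|---|---|---|
| 2.9.1 Primary outcome | Delivery at 20 weeks or later | A success, read literally |
| 2.9.2 Pregnancy loss rate | Intrauterine loss before 20 completed weeks | Not a loss |
| 2.9.2 Pregnancy complications | Includes perinatal death | Plausibly a complication |
| 2.7.5 Pregnancy visit | Stillbirth listed among losses | A loss |

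Appearing among the complications does not remove the event from the primary numerator, because section 2.9.1 contains no exclusion. Section 2.7.5 collects live-birth status, but the definition does not use it.

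**2. The plan's own sample size**

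Inputs from section 2.11: 2.5% vs 12.5%, two-sided α 5%, power 80%, dropout 15%.

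Unpooled formula: n = (1.960 + 0.842)² × (0.025 × 0.975 + 0.125 × 0.875) / 0.10² = 104.98, so 105 per group, as stated. Then 105 / 0.85 = 123.5, so 124, against the stated 125. The figures reproduce, and the definition does not enter them.

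**3. How many events could be misclassified**

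Expected events with 125 per arm: 125 × 0.025 = 3.1 control and 125 × 0.125 = 15.6 treatment. These use the planning rates, which section 2.11 words as applying within 6 months of randomization.

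The article gives no stillbirth rate. Assume that a share f of deliveries at or after 20 weeks is not live-born, and that 2.5% and 12.5% are delivery rates. Live birth rates are then 0.025(1 − f) and 0.125(1 − f).

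| f (assumed) | Misclassified, control (3.125f) | Misclassified, treatment (15.625f) | n per group, same formula |
|---|---|---|---|
| 0 | 0 | 0 | 105 |
| 0.5% | 0.02 | 0.08 | 106 |
| 1% | 0.03 | 0.16 | 107 |
| 2% | 0.06 | 0.31 | 108 |
| 5% | 0.16 | 0.78 | 112 |

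**4. Would a misclassified event change the test?**

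For equal arms of 125 and m total events, the uncorrected chi-squared is 250(a − b)² / [m(250 − m)].

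Near the planning rates:
- 3 vs 16: 250 × 169 / (19 × 231) = 9.63, P = 0.002
- 4 vs 16 (one control stillbirth counted): 250 × 144 / (20 × 230) = 7.83, P = 0.005
- 5 vs 16 (two counted): 250 × 121 / (21 × 229) = 6.29, P = 0.012

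For a smaller effect than planned:
- 3 vs 9: 250 × 36 / (12 × 238) = 3.15, P = 0.076
- 3 vs 10 (one treatment stillbirth counted): 250 × 49 / (13 × 237) = 3.98, P = 0.046

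Fisher's exact test, which section 2.16 also allows, gives 0.136 and 0.084 for the last two, so neither is significant. A single event matters only if the result already lies near the threshold.

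**The case against.** The strongest defence is that the intent is plain. The term being defined is live birth, the 20-week clause can be read as adding a gestational floor to it, section 2.7.5 collects whether the newborn was live-born, and section 2.10 times the final analysis after all live births. To score a recorded stillbirth as a live birth, an analyst would have to override both the outcome's name and a dedicated data item. Section 2.7.5 is also a list of events to record, not an outcome definition, so it may properly be broader than the loss outcome. Late fetal death also has a plausible place among the complications.

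Most of this stands. It shows that live-born infants were intended, so a reader should not infer that the trial set out to measure a different endpoint. It does not supply the missing condition: the operative sentence is complete as printed, and it is not detail that a journal article has deferred to a fuller document.

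Two further inferences are tempting and are not supported. The first is that the 20-week cut-off wrongly admits previable deliveries. The article gives no viability threshold, and a live-born infant just after 20 weeks can properly be a live birth under a 20-week rule. The second is that one or two misclassified deliveries would be likely to overturn the result. At the planning rates with 125 per arm, two misclassified control events still leave P = 0.012.

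**Conclusion.** The point holds as a defect in the wording of the primary endpoint. Section 2.9.1 omits the live-born condition, and sections 2.7.5, 2.9.1 and 2.9.2 do not agree on where a stillbirth at or after 20 weeks belongs.

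The expected numerical effect is small: under one event per arm for assumed non-live shares of 0.5% to 5%. The sample size is essentially unaffected, at 1 to 3 more couples per group for shares up to 2% and 7 more at the extreme of 5%. These figures rest on an assumed share, since the article gives none, and on the planning rates holding.

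What makes the defect worth correcting is its location. It sits in the primary numerator of an open-label trial, where one delivery is about a third of the roughly 3 control events expected. How such a delivery is classified should be settled by the protocol and not by judgement after allocation is known.

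**What to change.** Redefine the primary outcome in section 2.9.1 as delivery of at least one live-born infant at 20 or more completed weeks of gestation, determined from the live-birth status already obtained under section 2.7.5.

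Report non-live outcomes at or after 20 weeks separately: stillbirth, and any termination at that stage, since section 2.7.5 also lists selective abortion. Then align sections 2.7.5 and 2.9.2, so that each such pregnancy is handled the same way in recording, in the secondary outcomes and in the primary outcome.

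The cost is a short wording amendment, notified as section 2.13 provides. It needs no new visits, data items or couples. Section 2.10 plans no interim analysis, so the change can be made before outcomes are compared between groups.

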#### Secondary outcomes

2.9.2

(1) Semen parameters

1) sperm concentration: quantity of spermatozoa per unit of volume of semen, 10^6^/mL;

2) morphology: percentage of normal morphology;

3) motility: percentage of motile (including nonprogressive motile and progressive motile);

4) DFI: evaluate using SCSA test.

(2) Conception rate

Conception will be determined by a positive serum β-hCG measurement (β-hCG >10 mIU/mL).

(3) Pregnancy rate

Pregnancy will be characterized as an intrauterine pregnancy with confirmed fetal heart motion via transvaginal ultrasound.

(4) Pregnancy loss rate

Pregnancy loss will be refers to the intrauterine pregnancy lost before 20 completed weeks of gestation.

(5) Pregnancy complications

Including pregnancy diabetes, pregnancy induced hypertension, preeclampsia/preeclampsia, premature birth, congenital malformations, perinatal death, etc.

(6) Reproductive hormone

Including total testosterone, follicle stimulating hormone, luteinizing hormone, estradiol, progesterone, and prolactin.

(7) Adverse events.

### Interim analysis

2.10

We propose abstain from conducting an interim analysis, and the final data analysis will be carried out after all live births in the trial.

### Power calculation

2.11

Previous studies have shown that (33), among infertile men with abnormal semen, after taking placebo for 5 months, the live birth rate of spontaneous pregnancy of their female partners is 2.4%. It is assumed that in this study, the live birth rate of spontaneous pregnancy of couples in the waitlist-control group within 6 months after randomization is 2.5%, and 12.5% in the treatment group according to our clinical experience. Hence, the difference amounts to 10%, with two-sided α assigned to be 5% and β at 20% as the upper limit, while maintaining an 80% power and estimating a 15% dropout rate. Consequently, the sample size has been inflated from 105 to 125 per group, resulting in a total of 250 cases for the study.

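### The 80% power is calculated for a 6-month live birth rate, but the trial counts births from conceptions over 15 months, and no power is given for that outcome

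*Protocol article*

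**What the plan says.** Protocol article, section 2.11 (Power calculation), starts from a published live birth rate of 2.4% after 5 months of placebo. It then assumes rates "in the waitlist-control group within 6 months after randomization is 2.5%, and 12.5% in the treatment group according to our clinical experience". Its other settings are "the difference amounts to 10%, with two-sided α assigned to be 5% and β at 20% as the upper limit". Power is put at 80% and dropout at 15%. The result is 105 couples per group, raised to 125 per group, 250 in all.

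The rest of the article describes a longer observation period:

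- Section 2.1 (Trial design): 3 months of CHM or waitlist, then 12 months of follow-up, which makes 15 months.
- Section 2.4 (Exclusion criteria): couples planning IVF in the next 15 months are excluded.
- Section 2.7.5 (Pregnancy visit): "Female partners who become pregnant within 15 months after randomization will have pregnancy visit", and these visits continue until the pregnancy ends.
- Section 2.10 (Interim analysis): "the final data analysis will be carried out after all live births in the trial".
- Section 2.9.1 (Primary outcome): live birth is defined by gestational age at delivery (20 weeks or more), with no limit on when conception must occur.

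**The concern.** A power statement describes a test only if its rates are those of the outcome being tested. Here the rates belong to a 6-month window and the counting runs over 15 months. Nothing in the article links the two, and nothing limits the primary analysis to early conceptions. Table 1 has no 6-month milestone that would explain the choice.

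Both arms accumulate births after month 6. The control rate at 15 months should exceed 2.5%, because partners must ovulate and have a patent tube (section 2.3) and couples receive ovulation tests and timing advice throughout (section 2.6). The treated rate will also rise, by an amount that depends on how long any effect outlasts a 3-month course. The power for the primary outcome depends on that duration, about which section 2.11 makes no assumption.

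Two things are at stake. A null result could be read as coming from a trial with 80% power when that figure was never worked out for the outcome tested. And with two windows in the text of an unblinded trial, the choice of which rate to test could be made after results are known.

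**Working it through.** **Inputs from section 2.11:** 2.5% vs 12.5%, two-sided α 5% (z = 1.960), power 80% (z = 0.842), dropout 15%, 1:1 allocation.

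**1. The plan's own figure.** With the unpooled variance formula,

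n = (1.960 + 0.842)² × [0.025×0.975 + 0.125×0.875] / 0.10² = 7.849 × 0.13375 / 0.01 = 104.98, so 105 per group.

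This matches the stated value. The pooled-variance formula gives 108. For dropout, 105/0.85 = 123.5, which the plan rounds up to 125. Conversely, 125 × 0.85 = 106.25, so about 106 couples per arm are evaluable. The calculation is therefore sound for the 6-month rates.

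**2. Carrying the rates to 15 months.** The documents give no 15-month rates, so what follows is assumption: the 6-month rates apply at a constant pace.

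- Control: 1 − 0.975^(15/6) = 6.1%.
- Treated, if the 12.5%-per-6-months rate lasts m months and then falls back to the control rate: 1 − 0.875^(m/6) × 0.975^((15−m)/6).

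**3. Power at 106 per arm** (two-sided 5%; pooled variance under the null, unpooled under the alternative):

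Power = Φ{ [d − 1.960 × √(2p̄(1−p̄)/106)] / √([p₁(1−p₁) + p₂(1−p₂)]/106) }

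For m = 6, d = 0.0963, the null standard error is 0.0429 and the alternative standard error is 0.0424. This gives Φ(0.288) = 61%.

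| Assumption | Control | Treated | Power |
|---|---|---|---|
| As planned, 6-month rates | 2.5% | 12.5% | 79% |
| Advantage ends at 6 months | 6.1% | 15.8% | 61% |
| Advantage lasts 9 months | 6.1% | 20.2% | 86% |
| Advantage lasts 12 months | 6.1% | 24.4% | 96% |
| Advantage lasts 15 months | 6.1% | 28.4% | 99% |
| 10-point difference kept | 6.1% | 16.1% | 64% |

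The 79% in the first row reflects the pooled null variance; the unpooled formula in step 1 gives 80% at 105.

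**4. Break-even.** With a 6.1% control rate and 106 per arm, 80% power needs a treated rate of about 18.8%. That is a difference of about 12.7 points, or a relative risk of about 3.1 against the 5.0 in the plan.

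**5. Sensitivity to the control rate.** If a 10-point difference is kept while the control rate is set higher, power falls further: 53% at 10% vs 20% and 44% at 15% vs 25%. The 10% and 15% control rates are illustrative and have no source in the documents.

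**The case against.** The strongest reply is that a longer window need not cost power and may add to it. That stands. If the assumed treatment rate lasts 9 months or more, power exceeds 80%. A reader who holds the difference at 10 points and raises only the control rate might infer that the trial is underpowered. The documents do not support that: section 2.11 ties the 10 points to 6 months, and carrying them unchanged to 15 months lowers the relative risk from 5.0 to about 2.6 at a 6.1% control rate, and to 1.7 at 15% vs 25%.

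A reader might also infer that the planning rate describes nothing the trial can observe, since pregnant women are excluded and a term birth within 6 months of randomization is impossible. That goes too far. Section 2.11 is naturally read as births from conceptions within 6 months. The trial can count these, because partner pregnancy tests run through the whole schedule in Table 1 and conceptions are followed to their end.

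Compounding the 2.4% placebo figure over three 5-month periods would give about 7.0% for the control arm (1 − 0.976³). But the 5 months is stated as a duration of placebo, and the conception window behind the 2.4% is not given, so I place no weight on this figure.

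Finally, the planned test and the relative risk with its confidence interval are valid whatever power was stated. That is true and limits the harm. It does not make the 80% the power of the outcome being tested.

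**Conclusion.** The mismatch is certain: 6 months in section 2.11 against 15 months in sections 2.1, 2.4 and 2.7.5, with no 6-month limit in 2.9.1 and an analysis that waits for all births. It is an inconsistency of time window; the sample size arithmetic is correct for the rates it uses. The stated 80% does not apply to the primary outcome as counted.

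The size and direction of the error cannot be settled from the documents. Under constant rates and about 106 evaluable couples per arm, power runs from about 61% to 99% according to how long the treatment advantage lasts. It is about 64% if only a 10-point difference survives, and lower if the control rate exceeds 6.1%. All of these rest on the constant-rate assumption and on the plan's 12.5%, whose only stated basis is clinical experience.

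**What to change.** Choose one window and make sections 2.9.1 and 2.11 agree, before outcome data are examined.

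- **Option A (fits the trial as run).** In 2.9.1, define the primary outcome as live birth from a conception within 15 months of randomization. In 2.11, replace the 6-month rates with 15-month rates, state the assumptions behind them (including how long the effect is expected to last), and give the power of 250 couples over the full range, favourable scenarios included.
- **Option B (keeps the existing calculation).** Name live birth from a conception within 6 months of randomization as primary, leave the power calculation as it is apart from saying that the 6 months refer to conception, and make the 15-month rate secondary.

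Neither option changes the sample size, visits or treatment. The cost is rewording two sections and, under Option A, a stated power that may be less favourable than 80%.

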### Imputation procedure for missing data

2.12

We will document reasons for withdrawal in both randomization groups and qualitatively compare these reasons. The impact of any missing data on the results will be evaluated through sensitivity analysis using augmented data sets. To evaluate the effect of missing baseline data, we will employ the multiple imputation method with the missing-at-random assumption.

### Data management

2.13

Upon enrollment in the study, each participant will be assigned a unique identifier, which will be utilized across all data records to maintain participant confidentiality. Participant data will be managed using paper case record forms (CRF) and a web-based electronic database (ResMan). Following the collection of original participant documents, they will be transferred to the CRF. Subsequently, all data will be stored in the ResMan. Quality control of the data will be managed at two distinct levels: the investigators will be responsible for ensuring data accuracy as the initial level of control during record input into the CRF. The second level will involve regular data monitoring and validation via ResMan by DCC. Any changes to the current study protocol will be presented to the institutional review board, all trial participants, and trial researchers. Ultimately, individual participant data, excluding private information, will be available to the public within 6 months after the trial’s completion.

### Data monitoring and access

2.14

To ensure the safety of the study subjects, Data and Safety Monitoring Board (DSMB) will be established independently to review and interpret the data produced in this study. DSMB will oversee the study’s safety of and the integrity of data through routine video conferences or on-site inspections, offering recommendations on study conduct. In addition, DSMB will assess the advancement of the study, adjudicate adverse events, and determine on any potential premature closure of the study.

### Auditing

2.15

Audit trail is another measure to ensure data quality and integrity. Authorization is required for any additions, deletions, or modifications of information in the electronic system record. This study will use computer-generated audit trail with time stamp to track changes in electronic source files. In addition, controls will be implemented to verify the accuracy of the date and time in the electronic system, with only authorized personnel permitted to make adjustments to the date or time. Once any abnormal system date or time is detected, they will be immediately notified. Internal security measures will be established in the computerized system. The data will be stored at the servers located at Foshan Fosun Chancheng Hospital, under the supervision and access of DCC. To prevent data loss, regular backup records will be conducted.

### Data analysis

2.16

The outcomes were analyzed according to the intention-to-treat principle. The Kolmogorov–Smirnov test was used to test the normal distribution of continuous variables. Between-group comparisons were carried out by either a chi-squared test or Fisher’s exact test for categorical variables and by either Student’s t-test or Mann–Whitney U test for continuous variables. Comparisons of variables such as live birth rate, conception rate, pregnancy rate and pregnancy loss rate will include relative risk (RR) and 95% CIs in addition to the chi-squared test. A P-value <0.05 was considered to be statistically significant. All statistical analyses were performed using SPSS software version 23.0 (SPSS Inc., Chicago, IL, USA).

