### Inclusion criteria

2.3

(1) Couples inclusion criteria (29)

1) Infertility lasting 12 months or longer (whether primary or secondary);

2) Heterosexual;

3) Living together and able to have regular intercourse.

(2) Male inclusion criteria (29)

1) Older than or equal to 18 years old;

2) At least one of the following semen parameter deviates from the normal range in the semen analysis conducted over the past 6 months:

a. Sperm concentration ≤15 Million/ml;

b. Total motility ≤40%;

c. Normal morphology ≤4%;

d. DFI >25%.

3) Agree to provide semen samples as the proposed timeline at baseline, after 3 months of treatment, and after 3 months of follow-up;

4) Agree to sign the consent form.

(3) Female inclusion criteria (29)

1) ≥18 years and ≤40 years of age with normal ovarian reserve, defined as an early follicular phase FSH ≤10 IU/L, AMH ≥1.0 ng/ml, or antral follicle count greater than 10;

2) Regular menstrual cycle (25 to 35 days). Evidence to confirm ovulation, including biphasic basal body temperatures, positive ovulation predictor test, or serum progesterone level ≥3 ng/ml;

3) Evidence of at least one patent fallopian tube (determined by hysterosalpingogram or laparoscopy). 

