**Assessments:**							
Case history	√						
Vital signs	√	√	√	√	√	√	√
Anthropometric ^a^	√	√	√	√	√	√	√
Safety laboratory ^b^	√				√		√
Chromosomes of the peripheral blood	√						
Sex hormone steroids ^c^	√				√		√
Semen parameter analysis	√				√		√
Adverse event		√	√	√	√	√	√
Concomitant medications	√	√	√	√	√	√	√
Partner pregnancy test	√	√	√	√	√	√	√

^a^Anthropometric: weight, height, waist circumference, hip circumference. ^b^Safety laboratory: Blood routine test, thyroid function, renal and liver profile. ^c^Sex hormone steroids: Total testosterone, follicle stimulating hormone, luteinizing hormone, estradiol, progesterone, prolactin.

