#### Screening visit

2.7.1

(1) Obtain signed informed consent and detailed medical history collection;(2) Semen analysis: semen analysis after 2–5 days of sexual abstinence included standard measurements, such as volume, pH, count, and motility. Semen samples will be assessed in the hospital laboratory using WHO 5.0 criteria (31) for sperm morphology. In addition, DFI will be evaluated using Sperm Chromatin Structure Analysis (SCSA) test (32);(3) Laboratory examination: including reproductive hormone, blood routine test (BRT), thyroid function, liver function, kidney function, chromosome examination of peripheral blood.

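### Continuous secondary outcomes are compared by two-sample tests with no baseline adjustment named, although the same variables are measured at screening

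*Protocol article*

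**What the plan says.** Section 2.16 (Data analysis) gives the method for continuous variables in two consecutive sentences. The first reads "The Kolmogorov–Smirnov test was used to test the normal distribution of continuous variables". The second says that arms are compared "by either Student’s t-test or Mann–Whitney U test for continuous variables". No covariate, ANCOVA, mixed model or change-from-baseline variable is named. A relative risk with 95% CI is promised for live birth, conception, pregnancy, pregnancy loss and similar variables. No effect measure is stated for continuous outcomes.

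The outcomes concerned are listed in section 2.9.2: concentration, morphology, motility, DFI ("DFI: evaluate using SCSA test") and hormones ("Including total testosterone, follicle stimulating hormone, luteinizing hormone, estradiol, progesterone, and prolactin").

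All of them have a pre-treatment value:
- Table 1 ticks "Semen parameter analysis" and sex hormones at screening, month 3 and the 12-month follow-up.
- Section 2.7.1 adds that at screening "DFI will be evaluated using Sperm Chromatin Structure Analysis (SCSA) test", and that hormones are in the laboratory panel ("Laboratory examination: including reproductive hormone, blood routine test (BRT").
- Section 2.7.3 repeats semen analysis, DFI and hormones at month 3. Section 2.7.4 repeats semen analysis and DFI at the end of follow-up.

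In the analysis sections, baseline data appear only in section 2.12, where missing baseline values are to be multiply imputed.

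**The concern.** When an outcome is measured before and after treatment, the pre-treatment value is usually its best single predictor. A two-sample test of final values leaves that predictable part of the variation between men in the error term. It also lets any chance difference between arms at baseline pass into the estimated effect. A man can qualify on any one of four semen criteria (section 2.3), so each parameter is likely to mix normal and abnormal starting values.

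The second issue is the choice of test. If the Kolmogorov–Smirnov result decides between t and Mann–Whitney, the data decide whether the comparison concerns means or ranks. The answer could differ between parameters, or between the two follow-up times for one parameter.

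What is at stake is the precision and interpretability of the semen, DFI and hormone results. The primary outcome and the sample size are not affected.

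**Working it through.** **Inputs from the protocol article.** Section 2.11: live birth 2.5% against 12.5%, two-sided α 5%, power 80%, dropout 15%, 105 per group inflated to 125.

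**Assumed.** The correlation r between screening and follow-up values is not in the document; a range of 0.3 to 0.8 is shown. The variance is taken as equal at the two times.

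**Step 1: the plan's own figure.** With the unpooled formula,

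n = (1.960 + 0.842)² × (0.025 × 0.975 + 0.125 × 0.875) / 0.10² = 104.98, so 105 per group.

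For dropout, 105 / 0.85 = 123.5, so 124 against the stated 125. The figure reproduces closely. It rests on live birth alone; the article makes no power claim for continuous outcomes.

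**Step 2: reference case.** Evaluable men per arm: 125 × 0.85 = 106.25, taken as 106. A t-test of final values has 80% power for a difference of

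(1.960 + 0.842) × √(2/106) = 0.385 SD.

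**Step 3: relative variance of the treatment contrast** (test of final values = 1).
- ANCOVA: 1 − r²
- Change score: 2(1 − r)
- ANCOVA relative to change score: (1 − r²) / [2(1 − r)] = (1 + r)/2

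**Step 4: results at 106 per arm.** Power is for the 0.385 SD difference. The detectable difference is 0.385 × √(1 − r²).

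| r | ANCOVA variance vs final value | Power, ANCOVA | Detectable difference, ANCOVA (SD) | Power, change score | ANCOVA variance vs change score |
|---|---|---|---|---|---|
| 0.3 | 0.91 (−9%) | 83.6% | 0.367 | 65.8% | 0.65 (−35%) |
| 0.5 | 0.75 (−25%) | 89.9% | 0.333 | 80.0% | 0.75 (−25%) |
| 0.6 | 0.64 (−36%) | 93.8% | 0.308 | 87.9% | 0.80 (−20%) |
| 0.7 | 0.51 (−49%) | 97.5% | 0.275 | 95.1% | 0.85 (−15%) |
| 0.8 | 0.36 (−64%) | 99.7% | 0.231 | 99.3% | 0.90 (−10%) |

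A test of final values has 80% power in every row. ANCOVA has the smallest variance of the three throughout. A change score is worse than the final value when r is below 0.5.

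**Step 5: chance imbalance.** The 95% range for the baseline difference between arms is ±1.96 × √(2/106) = ±0.27 SD. A comparison of final values carries r times that difference into the result: from 0.3 × 0.27 = 0.08 SD to 0.8 × 0.27 = 0.22 SD at the edge of the range. The difference detectable with 80% power is 0.385 SD.

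**The case against.** The strongest reply is that nothing here is an error. Student's t and Mann–Whitney are valid for randomised arms, and the complaint is one of efficiency in secondary outcomes. That is right about validity, and it limits how far the point can be pushed.

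Several stronger readings are tempting and are not supported:
- **That baseline is discarded.** Section 2.16 names the tests but not the variable tested. A t-test on changes from baseline would fit the sentence and would use every screening value. Planned imputation of missing baseline data hints at some analytic use, without saying which. The text supports only that no baseline adjustment is named.
- **That the normality test is declared to be the selector.** This is the natural reading of two adjacent sentences, but it is not stated.
- **That a Mann–Whitney analysis yields no effect size.** A location shift with a CI can accompany it. The article simply states no effect measure for these outcomes.
- **That adjustment is worth 1.33 to 1.96 times the sample.** This holds for r of 0.5 to 0.7 (1/0.75 and 1/0.51) and only against final values. Against change scores the same r gives 1/0.75 = 1.33 falling to 1/0.85 = 1.18. At r = 0.3 the saving against final values is only 9%.
- **That baseline values are known to vary widely.** The document gives no SD, and section 2.4 excludes concentrations below 5 million/mL. The eligibility rule makes a mixture likely but does not measure it.

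A further reply is that a condensed article may leave covariates to a fuller document. That would excuse silence. Here the article does fix a method, and neither named test takes a covariate. In large samples ANCOVA is at least as efficient as a test of final values or of changes, so the recommendation holds whichever variable was meant.

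**Conclusion.** The point holds as a precision and pre-specification weakness in the continuous secondary outcomes. It is not a validity problem. Section 2.16 names covariate-free tests and no baseline adjustment for ten variables (four semen measures including DFI, and six hormones) that are measured at screening. It also implies a data-driven choice between means and ranks.

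The size depends on r, which the document does not give, and on which variable is tested. For r of 0.3 to 0.8 the avoidable variance is 9% to 64% if final values are compared, and 35% down to 10% if changes are compared. In neither case does adjustment lose. Live birth, its analysis and the 250-couple sample size are unaffected.

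A reader might infer that the planned comparisons are biased. They are not on average; a chance imbalance in the one trial that is run simply stays uncorrected.

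**What to change.** In section 2.16, for each continuous secondary outcome:

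1. Pre-specify ANCOVA of the month-3 value on arm and the screening value as the main comparison.
2. Analyse the end-of-follow-up value in the same way, or put both times into one baseline-adjusted mixed model. First reconcile the time of the last semen sample: the male inclusion criteria read "Agree to provide semen samples as the proposed timeline at baseline, after 3 months of treatment, and after 3 months of follow-up", while Table 1 and section 2.7.4 place it at the end of the 12-month follow-up. Table 1 also schedules hormones at that visit, whereas section 2.7.4 lists only semen analysis and DFI.
3. Fix in advance which variables are analysed on the log scale because they are expected to be right-skewed. The document gives no distributional data, so the list should be justified from outside the trial data.
4. Report the adjusted difference, or the ratio for logged variables, with its 95% CI.
5. State that no normality test selects the method, and keep the rank test as a sensitivity analysis.

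The cost is analysis wording only. The screening values are already collected, SPSS fits the model, and no visit, sample or participant is added.
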